## Health economics and costing procedures

All costing and economic evaluations will be primarily from the perspective of the health care system to enhance comparability with other studies. However, estimates of household costs of illness and deaths will also be included in certain cost effectiveness measures to reflect a societal perspective. The analysis will also explore the magnitude of household costs, potential for catastrophic costs of HIV and TB, and implications for universal access.

We will use a direct costing approach to assess incremental costs of the ICHF intervention in achieving the primary objective. Costs of diagnostic tests will be obtained from actual expenditures and price lists. Staff costs will be based on public sector remuneration scales for relevant staff, combined with observations, recording time use and services delivered, both to distinguish services from each other and to quantify, cost and exclude research specific activities. Travel costs will be based on logbooks and similar cost allocation approaches. Where any other substantial costs are identified and cannot be directly costed, e.g. management overheads, these will be estimated using step down methods. Household members will be asked at interview about direct and indirect costs (e.g. lost income) of illness and accessing healthcare, and about effect on various household asset holdings (appliances, cellphones etc.) to explore dissaving and potential for catastrophic costs.

The principal cost effectiveness indicators will be incremental costs per person diagnosed with HIV and/or TB, and importantly cost per person linked to HIV and/or TB care through the ACF intervention in each setting, and cost per incident TB case and death avoided, as these could inform immediate, large-scale policy choices. Further indicators such as estimated incremental cost per life year saved or per TB treatment completion will be generated if the frequency and profile of reported clinical outcomes support this. In addition, we will measure health-related quality of life of household members using the EuroQol EQ-5D adjusted for Southern Africa (Maheswaran et al. 2016)

Records of health service utilization (in-patient days and outpatient visits) for each group will be combined with unit costs for each type of care derived from step down costings in relevant facilities to obtain indications of possible cost savings and net costs. Sensitivity analyses will be undertaken to assess strength and robustness of cost effectiveness findings, and aggregated and disaggregated measures of costs will be reported to aid comparisons with other interventions and settings. Incremental cost effectiveness ratios will be compared to South African benchmarks and other measures (e.g. per capita GDP) to facilitate interpretation for policymakers.

# Study Definitions

**Households:** Physical dwelling structures comprising of all rooms under a contiguous roofed area linked by doorways or windows through which air can pass or potentially can pass.

**Household members:** All individuals who shared household airspace for lengthy periods – either slept overnight at least once, or shared at least two meals in the same household as the index case - in the 14 days prior to the index case’s diagnosis of TB

**Incident bacteriologically-confirmed TB** will be defined by a household contact who has documented evidence of at least one of any of the following: sputum smear positive for acid-fast bacilli; or culture with growth of Mycobacterium tuberculosis confirmed on speciation; or positive Xpert MTB/Rif result; or histology or cytology suggestive of TB, regardless of whether TB treatment was initiated. We will restrict incident cases to those diagnosed on a specimen taken at least 2 months after the initial baseline household contact.

**Incident bacteriologically unconfirmed TB** will be defined by a household contact without bacteriologically-confirmed TB but who has at least one of the following: TB treatment registers, or patient held TB treatment cards indicate TB treatment was initiated; or either died or was discharged from hospital with a diagnosis of TB without laboratory confirmation.

**All forms of TB** will be defined in individuals with either bacteriologically-confirmed, or bacteriologically-unconfirmed TB.

**Prevalent *Mycobacterium tuberculosis infection*** will be defined by the presence of skin induration reaction measured to be >10mm using technique recommended by the International Union Against Tuberculosis and Lung Disease at 48-72 hours after subdermal injection of 2 TU in 0.1 ml PPD RT23/Tween 80 in children younger than 7 years of age.

**Prevalent previously undiagnosed HIV infection** will be defined by household members who, at month 15 assessment, test positive for HIV using a serial rapid diagnostic test algorithm infection, having reported never previously tested positive for HIV.

**Prevalent previously undiagnosed and untreated HIV infection** will be defined by household members who, at month 15 assessment, test positive for HIV using a serial rapid diagnostic test algorithm infection and report not currently taking antiretroviral therapy.

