**Sputum Collection**

To avoid bias related to collecting better quality sputum samples from symptomatic patients, we will collect one spot sputum sample from all household members capable of producing a sputum sample, before we ask about TB symptoms. Prior to producing a sputum specimen household members will be asked to drink a cup of water and rinse out their mouths, then take four deep breaths prior to giving a good cough effort. If small volumes of sputum are obtained, we will allow up to three hours for the collection of a spot sputum specimen. This specimen will be subjected to Xpert MTB/Rif (or the at time-of-study current version of the usual first line TB lab test in the public sector) and liquid mycobacterial culture at public sector laboratories. Single sputum specimens will be at least 3ml and at the lab will be mixed with decontaminant as per standard operating procedures in the two public sector laboratories we will send specimens to - then split into two: Xpert MTB Rif (with subsequent addition of buffer) and immediate liquid culture in the MGIT automated system as per current protocols in public sector mycobacterial laboratories. We will record the cycle threshold number of the Xpert and the time-to-positive in liquid culture. Sputum samples will be immediately stored and transported in coolboxes at 4ºC to public sector laboratories for testing. Anyone who tests positive for *M tuberculosis* will be immediately referred to their chosen public sector clinic for TB treatment initiation with a clear referral letter. For those who are Xpert MTB/Rif negative, HIV-negative and over 5 years of age a tuberculin skin test will be performed with the needle of the syringe parallel to the long axis of the arm at this initial visit and read 48 – 72 hours later using the ball-point pen to mark the widest transverse diameter measured with the reverse calliper method in millimetres. No induration will be documented as 0mm.

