All intervention households will be visited once at approximately three months after the initial assessment. This visit will be offered because our previous data suggests that a significant proportion of household members with either TB, or HIV, diagnosed at the baseline household visit, do not access care or treatment. Patients not accessing TB treatment, ART or IPT care will be reassessed and assisted to start appropriate treatment, with study staff attempting to overcome access barriers identified by this group. In addition, we will reassess whether those with hypertension or those diagnosed with type 2 diabetes mellitus were started on appropriate therapy and are at this visit controlled or have a plan for future care. Household members requiring other assistance or care will receive supported access to their local health facility or to the Department of Social Development to access social grants. Moreover, at this visit a TB symptom screen on all available household members not on TB treatment will be done, with investigation of those with symptoms, using Xpert and TB culture. We will not visit the household again to interview household members not present at this single final intervention visit.

All visits will be recorded including the number and level of staff members and the purpose and duration of the visit.

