Finding households of index cases can be time consuming, and ideally non-intervention households should be as similar to intervention households as possible. To try and ensure that non-intervention households are not visited by teams who have been searching for a household for longer periods than intervention households where locations are known, 2-6 months prior to the final outcome visit – if resources permit - we will send a study staff team member to locate the non-intervention houses and reintroduce the study to at least one household member. Apart from confirming the address using the what3word App, no data will be recorded.

At the final outcome visit, Research Assistants will revisit all households 1) trace all household participants, ascertain vital status and brief verbal autopsies for those who have died; 2) record episodes of TB and HIV diagnosis and when they occurred, treatment and other hospitalizations from verbal report and inspection of patient-held records; and 3) investigate participants with symptoms of TB (any of: cough, fever, weight loss, night sweats) by collecting sputum for smear microscopy, sputum culture and Xpert; and 4) encourage and offer repeat HIV testing to participants negative or not previously tested at baseline; and 5) conduct a prevalence survey for latent TB infection by testing all children under 14 years old with the tuberculin skin test, read at 48-72 hours later as described previously; 6) a livestock survey will also be done on a sub-sample of 300 households (150 households per site) assessing exposure to domestic pets and livestock and consumption of raw milk.

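### A positive smear alone confirms incident TB even when valid Xpert and culture results from the same episode do not show M. tuberculosis

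*Protocol*

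**What the plan says.** Protocol, Study Definitions: incident bacteriologically-confirmed TB applies to "a household contact who has documented evidence of at least one of any of the following", and the list includes "sputum smear positive for acid-fast bacilli; or culture with growth of Mycobacterium tuberculosis confirmed on speciation; or positive Xpert MTB/Rif result", then histology or cytology. It applies whether or not TB treatment was started. The timing limit is: "We will restrict incident cases to those diagnosed on a specimen taken at least 2 months after the initial baseline household contact". All forms of TB is defined as confirmed plus unconfirmed TB, so every confirmed case belongs to it.

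Protocol, Outcomes: the primary outcome, TB free survival, is measured once with TB by any diagnostic method and once with bacteriologically-confirmed cases only.

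Tests on study sputum (Protocol, Trial Procedures):
- Baseline, intervention arm: "This specimen will be subjected to Xpert MTB/Rif", plus liquid culture. No smear.
- Month 3, intervention arm, symptomatic members: "with investigation of those with symptoms, using Xpert and TB culture". No smear.
- Month 15, both arms: "investigate participants with symptoms of TB (any of: cough, fever, weight loss, night sweats) by collecting sputum for smear microscopy, sputum culture and Xpert".

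At month 15 staff also "record episodes of TB and HIV diagnosis and when they occurred, treatment and other hospitalizations from verbal report and inspection of patient-held records", so routine-care results can supply events too.

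The Background section faults smear for insufficient sensitivity in contact tracing. The protocol gives no smear specificity and no rule for discordant results.

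**The concern.** The definition applies two standards of species identification. A culture counts only if it speciates as M. tuberculosis. A smear counts without any species evidence, and still counts when the culture from the same episode grows a different species. A month-15 contact who is smear-positive and Xpert-negative, and whose culture grows a non-tuberculous mycobacterium or nothing, is therefore a confirmed primary event. Because all forms contains confirmed, that contact is an event in the other version of the primary outcome as well, even if nobody treated them for TB. Neither version is protected.

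The month-15 screen covers both arms in the same way. False events from it should be about equally frequent in each arm, which moves the rate ratio towards no effect. TB is rare among those screened, so a few such events can matter.

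**Working it through.** The protocol has no figure of its own on this point, so there is none to reproduce. The check has a logical part and an arithmetic part.

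**Logic.** Suppose all three month-15 results are valid. If Xpert or culture shows M. tuberculosis, the contact is confirmed with or without smear. Smear changes the classification only when both of the others fail to show M. tuberculosis. In that setting, smear's unique contribution is exactly the discordant group.

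**Inputs from the protocol**
- 2,400 households, 1,200 per arm if allocation is 1:1 (assumed; the ratio is not stated), with a mean size of 5.5: 1,200 × 5.5 = 6,600 members per arm.
- Annual incidence: mean of the three printed district rates, reading the last as per 100,000: (937 + 686 + 371)/3 = 664.7 per 100,000.
- Thirteen months of follow-up. The 30% difference is read as a rate ratio of 0.70.

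Control events: 6,600 × 0.006647 × 13/12 = 47.5. Intervention events: 0.70 × 47.5 = 33.3. Total: 80.8.

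These inputs do not reproduce the stated 80% power. With 654 per 100,000 (mean of 937 and 371) and 0.3 read as a between-cluster coefficient of variation, power is about 35%. That is a separate matter; the event counts serve here only as a scale.

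**Inputs assumed** (none is in the protocol): share symptomatic at month 15, 5% to 20%; share of those giving sputum, 70% to 100%; smear specificity, 98% to 99.9%; equal numbers of false events in both arms; every false-positive smear has valid, non-supporting Xpert and culture results.

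**Formulas**
- False events per arm: FP = 6,600 × symptomatic × yield × (1 − specificity).
- Observed ratio: RR = (33.3 + FP)/(47.5 + FP).
- Rise in events needed: A = (ln 0.70 / ln RR)².
- Rise in events observed: B = (80.8 + 2 FP)/80.8.
- Net loss of information: A/B.

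| Symptomatic | Yield | Specificity | FP per arm | Observed RR | A | B | A/B |
|---|---|---|---|---|---|---|---|
| 5% | 70% | 99.9% | 0.23 | 0.701 | 1.01 | 1.01 | 1.01 |
| 5% | 100% | 99.5% | 1.65 | 0.710 | 1.09 | 1.04 | 1.04 |
| 10% | 70% | 99.5% | 2.31 | 0.714 | 1.12 | 1.06 | 1.06 |
| 10% | 70% | 99% | 4.62 | 0.727 | 1.25 | 1.11 | 1.12 |
| 10% | 100% | 99% | 6.60 | 0.737 | 1.36 | 1.16 | 1.17 |
| 20% | 70% | 98% | 18.48 | 0.784 | 2.15 | 1.46 | 1.47 |
| 15% | 100% | 98% | 19.80 | 0.788 | 2.25 | 1.49 | 1.51 |

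The rows span a tested share of 3.5% (5% × 70%) to 15%. The extreme corner, 20% symptomatic with full yield and 98% specificity, gives FP = 26.4, RR 0.81 and a net factor of 1.68.

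**Sensitivity to the true event count.** At 528.5 per 100,000 (mean of 686 and 371), the 20%/70%/98% row gives RR 0.80. At an assumed contact incidence of 1,940 per 100,000 (138.7 and 97.1 events), the same row gives RR 0.735, and FP = 4.62 gives 0.71.

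**The case against.** A good case can be made for listing smear. The definition accepts any documented result, and TB episodes are also collected from patient-held records. A routine-care smear can therefore be the only evidence of a real case at any time from month 2. The protocol also accepts smear alone as laboratory confirmation for older index cases, so the outcome definition follows its own standard. This stands, and the fix keeps such smears.

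Three stronger readings are tempting and are not supported:
- A reader might infer that smear mainly adds false events. The protocol gives nothing on specificity. Its remark on low sensitivity limits how many true cases smear can add but does not show that positive smears are false. A contaminated culture beside a missed Xpert can leave a true case smear-only.
- A reader might infer that the confirming tests change over follow-up to the detriment of the comparison. Baseline specimens fall before the incident window, month 3 is an intervention-arm visit, and the only study testing done in both arms uses one test set. The definition itself never changes.
- A reader might take the rise in events needed (column A, 1.09 to 2.25 over specificities of 98% to 99.5% and 5% to 15% tested) as the cost. The false events also raise the number observed, so the net cost is about 1.04 to 1.51 over the same rows.

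A sensitivity analysis without smear-only cases could well sit in an analysis plan that is not shown. The definition, however, is fixed in the protocol, and as written it counts the discordant case.

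**Conclusion.** The point holds in a limited form. The definition confirms TB on smear against two valid species-specific results, and such events reach both versions of the primary outcome. If they are similar in number in the two arms, the bias is towards no effect.

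The size is not known. With 3.5% to 15% of members tested at month 15 and specificity of 98% to 99.9%, a true ratio of 0.70 would appear as about 0.70 to 0.79. The net information loss runs from negligible to about 1.5-fold, and is about 1.17-fold at 10% symptomatic, full yield and 99% specificity. It is smaller if deaths count as events in TB free survival, or if TB incidence in contacts exceeds the district rates; the Executive Summary reports substantially more undiagnosed TB in contacts than in households without an index case. The change is worth making because it costs little and uses results already collected, not because the dilution has been shown to be large.

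**What to change.** Add to the definition of incident bacteriologically-confirmed TB in Study Definitions:
- A positive smear confirms TB if Xpert or culture from the same episode is positive for M. tuberculosis, or if valid Xpert and culture results are not available (not done, contaminated or failed).
- A smear-positive episode with valid Xpert and culture results, neither showing M. tuberculosis, is not confirmed. It counts under all forms only if it meets the existing criteria for unconfirmed TB: treatment started, or death or hospital discharge with a TB diagnosis.
- State the mixed case explicitly. Under the wording above, one valid non-supporting result with the other missing leaves the smear as confirmation.

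Report the number of smear-only cases by arm.

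The cost is a few lines of text, with no new test or visit. The downside is that a rare true case missed by both Xpert and culture leaves the confirmed version. It stays in all forms if it meets the unconfirmed criteria.

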**Secondary objectives:**

1. To assess the effectiveness of isoniazid preventive treatment on new cases of TB in HIV-seronegative individuals who are tuberculin skin test positive.
2. To compare the yield and costs of IHCS versus standard of care in identifying undiagnosed cases of TB and undiagnosed or untreated HIV
3. To compare rates of linkage to TB treatment between participants identified with TB through IHCS and standard of care
4. To explore perceptions and acceptability of doing home visits with household members

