**HIV testing**

All household members will be offered HIV testing after counselling, in the first instance using a serial rapid diagnostic test algorithm, the kits for which will be provided provided by the Provincial Departments of Health. Research Assistants trained and accredited in HIV testing and counselling. In line with recommendations in the World Health Organization’s HIV Testing Services Guidelines 2015, a negative A1 test result will diagnose participants as HIV-negative. Positive results to both Tests A1 and the confirmatory A2 test will diagnose participants as HIV-positive. Where results to Test A1 and A2 are discrepant, both tests will be repeated, and followed by a tie-breaker using a laboratory-based 4^th^ Generation ELISA (anticipated in <1 per 1000 participants). Couples testing will be provided if requested.

Children under 18 months of age will have a dried blood spot sample taken for HIV PCR testing as per South African National Guidelines, with testing performed at the National Institute for Communicable Diseases. Results-based post-test counselling will be offered individually in a private setting out-of-earshot and out of sight of other household members.

Participants declining HIV testing may be offered alternative laboratory-based HIV testing on either a blood specimen or an oral fluid specimen using OraQuick, OraSure Technologies –depending on their availability, with communication of results within one week, but if still reluctant to be HIV tested, will be asked to provide an anonymous oral fluid sample for HIV testing for study purposes. Those who request anonymous testing without receipt of results and those who refuse HIV testing will be encouraged to go to a HIV testing facility for testing.

All participants who test HIV positive will be referred to their nearest clinic for initiation of ART. We will draw blood specimen for CD4 count estimates -if still required by National Guidelines as these are expected to change to a test and treat approach in the near future – as soon as the participant is diagnosed with HIV. Participants who test HIV positive will receive supported access to HIV treatment, prearranged by the study at their nearest HIV care clinic.

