## Outcomes

*Primary trial outcomes*

1. Comparison between trial groups of TB FREE SURVIVAL from two months after randomisation – to the final ascertainment visit among all household members identified at baseline – a total of 13 months. We will measure this in two ways; firstly, including TB irrespective of the diagnostic method and secondly, including only bacteriologically-confirmed cases of TB.

*Secondary trial outcomes*

1. Comparison between trial groups of the incidence of all-forms of TB over months 2-15 among household members identified at baseline
2. Comparison between trial groups of the proportion of TB cases with diagnostic delay (defined as number of days between onset of symptoms and diagnosis of anti-tuberculosis treatment) among household members identified at baseline and diagnosed with TB between baseline and month 15
3. Comparison between trial groups of the prevalence of TB infection measured by tuberculin skin test reactivity >10mm at month 15 among household children identified at baseline and aged under 14 years of age. Analysis will be done overall and stratified by age.
4. Comparison between trial groups of the prevalence (reported as a percentage of those tested) of previously undiagnosed and untreated HIV infection among household members identified at baseline and again at month 15.
5. Comparison between trial groups of the cumulative incidence of all-cause mortality among all household members identified at baseline between baseline and month 15.
6. Comparison between trial groups of the cumulative incidence of TB- and HIV-related non-traumatic mortality among all household members identified at baseline between baseline and month 15.
7. Estimation of the cost-effectiveness of the intensified housed TB and HIV case-finding and prevention activities compared to the enhanced standard of care from a societal perspective.

*Exploratory outcomes*

1. Cohort analysis of the incidence of bacteriologically-confirmed, and all-forms of tuberculosis among intervention group household members receiving and not receiving isoniazid preventive therapy stratified by HIV serostatus.
2. Cohort analysis of the proportion of household members in the intervention group with previously undiagnosed HIV infection identified at baseline who successfully initiate antiretroviral therapy by month 15.

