Statistical analysis will be conducted using R (The R Foundation for Statistical Computing, Vienna, Austria) or Stata (StatCorp, College Station, Texas, USA). All analyses will employ statistical methods that allow for within-cluster (household) correlations. For all analyses, a 2-sided p-value<0.05 will be considered a statistically significant difference. No adjustment will be made for multiple testing.

Although baseline imbalance between the two intervention groups is unlikely due to the large sample size of this cluster randomised trial, the following situations will be considered as demonstrating imbalance in baseline covariates:

• More than 5% difference between the two arms in: % male and proportion of index cases with bacteriologically-confirmed pulmonary tuberculosis.

• More than 5 years difference in mean age.

• More than 1 person difference in mean number of household members

If there is no unbalance in covariates, study conclusions will be based on the unadjusted analysis described below. Otherwise, study conclusions will be based on analysis adjusted for imbalanced covariates as described below.

For the primary trial outcome (TB free survival), Poisson regression with random effects to account for clustering at the household level, will be used to estimate a rate ratio, 95% confidence interval and p-value for the effect of the intervention. To allow for the stratified randomisation by district, a fixed effect term for district will be included in the regression model. Where imbalance exists between trial groups (as defined above), these covariates will also be included in the regression model.

Analysis of secondary- and exploratory outcomes will follow a similar approach, except where binomial outcomes are assessed (e.g. proportion of child household members with MTB infection; proportion of household members with undiagnosed or untreated HIV), in which case we will use logistic regression with random effects to account for household clustering. For secondary outcome 5 (community HIV load), we will calculate this as the fraction of HIV-positive individuals with a measured viral load who have detectable viraemia multiplied by the number of individuals testing HIV-positive and divided by the total population with a measured HIV status.

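### The secondary HIV outcome is labelled undiagnosed and untreated but defined as positive and off ART, and the month-15 testing rule, read literally, counts the two arms differently

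*Protocol*

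**What the plan says.** The Outcomes section lists, as a secondary outcome, the prevalence of "previously undiagnosed and untreated HIV infection among household members identified at baseline and again at month 15", with the denominator "reported as a percentage of those tested". The Executive Summary uses the same *and* wording.

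Study Definitions holds two adjacent HIV definitions, both at month 15:

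- Previously undiagnosed HIV: a positive rapid-test result, "having reported never previously tested positive for HIV".
- Previously undiagnosed and untreated HIV: members who "test positive for HIV using a serial rapid diagnostic test algorithm infection and report not currently taking antiretroviral therapy".

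The secondary objectives speak of "identifying undiagnosed cases of TB and undiagnosed or untreated HIV". Statistical analysis twice gives, as an example of a binomial outcome, the "proportion of household members with undiagnosed or untreated HIV".

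On testing, the intervention arm's baseline visit provides that "All household members will be offered HIV testing after counselling". The enhanced standard-of-care arm has one contact with the index case, a telephone call about a week later, and no further contact until the outcome visit. At that visit, for all households, staff "encourage and offer repeat HIV testing to participants negative or not previously tested at baseline".

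**The concern.** There are two linked problems.

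The first is the label. A person who has known of their HIV for years and is not on ART meets the second definition and would be reported as previously undiagnosed. The outcome lists and the analysis text then point to different sets of people, so the same data can yield two prevalences under one outcome name.

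The second is who can enter the count. The definition requires a positive test at month 15. The people to whom that test is offered depend on a baseline study test that only one arm received. If the rule is followed as written, part of any difference between arms would come from counting and not from the intervention.

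**Working it through.** The protocol gives no HIV prevalence among contacts, no ART coverage and no target for this outcome, so there is no stated figure to reproduce.

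**Step 1. How many numerators are there?** Someone who does not know they are HIV-positive is, in practice, not on ART. The set *undiagnosed or untreated* is therefore the set *positive and not on ART*, which is the second definition. The set *undiagnosed and untreated* is in practice the set *undiagnosed*, which is the first definition. That leaves two numerators:

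| Place | Wording | Set in effect |
|---|---|---|
| Executive Summary; Outcomes | and | undiagnosed |
| Study Definitions, second HIV definition: title | and | undiagnosed |
| Study Definitions, second HIV definition: rule | positive, not on ART | untreated |
| Secondary objectives; Statistical analysis (twice) | or | untreated |

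**Step 2. How far apart could they be?** All inputs here are assumed: HIV prevalence 15%, a share u = 20–40% of positives undiagnosed, and a share o = 15–30% of known positives off ART.

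- Undiagnosed: 0.15u = 3.0% to 6.0%.
- Positive and off ART: 0.15u + 0.15(1−u)o. The lowest value is 0.030 + 0.018 = 4.8% and the highest is 0.060 + 0.027 = 8.7%.
- Ratio of the two: from 0.0735/0.060 = 1.2 to 0.066/0.030 = 2.2.

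This is one pooled population. It shows that the wording matters and says nothing about bias between arms.

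**Step 3. Who is counted in each arm at month 15, reading the testing rule literally?**

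- Control, known positive, off ART: no baseline study test, so offered the test and counted.
- Intervention, positive at the baseline study test, off ART at month 15: neither negative nor untested at baseline, so not offered the test, and absent from numerator and denominator.
- Intervention, not tested at baseline: offered the test and counted, as in controls.

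The second group will not be empty. In explaining the three-month visit, the protocol says its earlier data show that many people diagnosed at a baseline visit do not reach care.

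**Step 4. Direction.** Let x of n retained intervention members be counted, and let y of m dropped members be off ART. Dropping them lowers the prevalence whenever y/m exceeds x/n. Since the dropped group are all HIV-positive and the retained group mostly are not, this is the likely case.

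**Step 5. An illustration per 1,000 members per arm.** All inputs are assumed:

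- 60 undiagnosed and 30 known positive off ART at the start;
- 75% of intervention members tested at baseline;
- ART started by 60% of positives identified at baseline in the intervention arm, and by 30% of known positives otherwise;
- 10% of undiagnosed controls diagnosed through the letter, of whom 60% start ART.

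The counts are:

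- Control: known off ART 30×0.7 + 60×0.1×0.4 = 23.4; undiagnosed 60×0.9 = 54; total 77.4.
- Intervention, literal rule: 30×0.25×0.7 + 60×0.25 = 5.25 + 15 = 20.25. Ratio 20.25/77.4 = 0.26.
- Intervention, baseline positives counted: add (30+60)×0.75×0.4 = 27, total 47.25. Ratio 47.25/77.4 = 0.61.

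Here y/m = 27/67.5 = 40%, against x/n = 20.25/932.5 = 2.2%. Removing the 67.5 from the denominator as well moves the literal ratio only to (20.25/932.5)/(77.4/1000) = 0.28. People already on ART are left out of the illustration.

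Over a grid of assumed inputs (undiagnosed 3–10%, known off ART 1–5%, baseline testing 60–90%, ART uptake 10–30% in controls and 40–80% in the intervention arm, letter diagnosis 10–30%), the ratio of counts is 0.10–0.48 (median 0.27) under the literal rule. It is 0.30–0.93 (median 0.63) with baseline positives counted. Controls hold 72–96% of the counted known-positive, off-ART people under the literal rule, and 15–72% otherwise.

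**The case against.** The strongest reply is that most of the protocol already agrees. The objective, the rule in the second definition and both analysis passages all describe people who are positive and not on ART; the outlier is the word *and* in the outcome lists and in the definition's title. The undiagnosed outcome also has its own proper definition alongside. This stands, and it limits the first problem to a label that needs reconciling. A reader might infer three different numerators; there are two.

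Counting known positives off ART is also not an error in itself. Untreated HIV is a stated target and supported access to ART is part of the intervention, so fewer untreated people in that arm could be a real effect. This stands too. The fault is in reporting them as undiagnosed.

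A reader might go further and infer that the definition inflates the outcome mainly in controls. The protocol does not support that as a general statement. The asymmetry comes from the month-15 testing rule, not from the definition's wording. The rule does not say that only those groups may be tested, and intervention members who missed or declined the baseline test remain eligible. If baseline positives are tested or carried forward, the control share in the grid falls to 15–72% and its direction is no longer fixed.

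**Conclusion.** The concern holds in two parts. The label and the definition disagree: known positives off ART would be reported as previously undiagnosed, and the protocol uses *and* in some places and *or* in others. This rests on the text alone.

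The testing rule and the definition, taken together and literally, also count the arms differently, in a direction that would favour the intervention. This is conditional on the testing rule being applied as written. Its size cannot be derived from the protocol, and every figure above beyond the wording comparison rests on assumed inputs.

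This is one of seven secondary outcomes in the Outcomes section. TB-free survival is unaffected.

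**What to change.** Report two month-15 outcomes:

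- **(a) Previously undiagnosed HIV**, using the first existing definition unchanged.
- **(b) Untreated HIV**, meaning HIV-positive and not on ART, by relabelling the second definition. Do not add the never-previously-positive condition to it: that would practically duplicate (a) and remove the known positives off ART whom (b) is meant to count.

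For (b), include everyone positive at the study's baseline test in the denominator, and in the numerator if off ART at month 15, without retesting. State one counting rule that applies to both arms.

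Use the same wording in the Executive Summary, the secondary objectives, Outcomes, Study Definitions and both places in Statistical analysis.

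The cost is mainly wording. The existing definitions already rely on reported prior testing and current ART. The one practical requirement is that ART status at month 15 is recorded for baseline positives as well.
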